### Provisions for posttrial care {30}

All participants will no longer receive the intervention measures of this study at the end of 12 weeks. Endocrinologists will be responsible for the follow-up of all research patients, and whether to continue with blood sugar lowering treatment depends on the patient’s condition.

### Outcomes {12}

The primary outcomes are severity of NAFLD. The secondary outcomes include HbA1c, and homoeostasis model-insulin resistance index (HOMA-IR), an indicator of insulin resistance, will be calculated via formula as follows: [fasting glucose (nmol/L) × fasting insulin (mU/mL)/22.5], fasting blood glucose, 2-h postprandial blood glucose, BMI, waist circumference(WC), total cholesterol, low-density lipoprotein cholesterol, high-density lipoprotein cholesterol, triglycerides, and systolic and diastolic blood pressure.The primary and secondary outcomes will be reevaluated at the end of 12 weeks. Supplementary Table S1 presents the outcome definition.

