**Methods:**

Participants will be recruited in this single-center, randomized clinical trial through telephone interview. All participants will be assigned randomly at a 1:1:1 ratio to three groups and treated with lifestyle modification including calorie-restricted dietary and exercise therapy, 500–2000 mg/day metformin, or treated with both lifestyle modification and 500–2000 mg/day metformin (the co-intervention group) for 12 weeks. The primary outcomes are changes in glycemic control and severity of fatty liver from baseline to 12 weeks of follow-up.

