### Objectives {7}

The primary objective of this randomized clinical trial is to evaluate the efficacy of lifestyle modification combined with metformin in NAFLD patients with newly diagnosed type 2 diabetes.

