### Sample size {14}

The sample size was calculated according to changes in the primary outcome measure (12-week change in HbA1c with *α* = 0.05, *β* = 80%). A sample size of 31 individuals per group will be selected with mean changes of 0.4 and standard deviation of 1.5 and a 20% attrition rate [10]. It is calculated by PASS 15.

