#### Hepatic steatosis

Transient elastography (FibroScan) would be performed after 8-h overnight fasting to assess hepatic steatosis and fibrosis according to liver stiffness measurements (LSM) and controlled attenuation parameter (CAP) score. The severity of fatty liver will be evaluated at baseline and 12 weeks later.

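### The article designates the primary outcome in three conflicting ways, so the outcome declared primary has no sample-size basis and the outcome that was sized is listed as secondary

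*Protocol article*

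**What the plan says.** Three sections of the protocol article designate the primary outcome, and all three are current text.

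- Abstract, Methods: "The primary outcomes are changes in glycemic control and severity of fatty liver from baseline to 12 weeks of follow-up". Two domains, glycaemia and liver, are primary.
- Outcomes {12}: "The primary outcomes are severity of NAFLD. The secondary outcomes include HbA1c". The liver alone is primary and HbA1c is secondary. The same section adds: "Supplementary Table S1 presents the outcome definition". That table is not shown.
- Sample size {14}: the number was "calculated according to changes in the primary outcome measure (12-week change in HbA1c", followed by the planning values. HbA1c is the primary, in the singular.

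The other sections do not settle it. The primary objective is to "evaluate the efficacy of lifestyle modification combined with metformin in NAFLD patients with newly diagnosed type 2 diabetes", with no endpoint named. Statistical methods {20a} sets one significance level of 0.05 and no order among outcomes. Blinding {17a} {17b} states that the trial is open.

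**The concern.** The primary outcome fixes three things: what the sample size has to support, where the 5% error is spent, and which result carries the conclusion. Here all three depend on which section is read. A reader who follows Outcomes {12} finds a liver primary for which the article gives no planning difference, SD or power. A reader who follows Sample size {14} finds a trial sized on a measure that Outcomes {12} ranks as secondary. A reader who follows the Abstract finds two primaries and no statement of whether one or both must succeed.

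Because allocation is known to everyone, an unresolved primary is more exposed than it would be in a blinded trial. If the glycaemic and liver results disagree, the published text supports calling either one decisive.

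**Working it through.** **1. The three designations side by side**

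| Section | Glycaemia | Liver |
|---|---|---|
| Abstract, Methods | primary (as glycaemic control) | primary |
| Outcomes {12} | HbA1c secondary | primary |
| Sample size {14} | 12-week change in HbA1c, sole primary | not mentioned |

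HbA1c is primary in the third row and secondary in the second. Any single true designation leaves at least two rows needing correction.

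**2. The plan's own figure**

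Inputs from Sample size {14}: difference 0.4, SD 1.5, alpha 0.05 (taken as two-sided), 80% power (the article prints this as beta), 20% attrition. The stated result is 31 per group.

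- n per group = 2 × [SD × (1.96 + 0.84) / difference]² = 2 × (1.5 × 2.80 / 0.4)², which gives 221 with unrounded normal quantiles.
- After attrition: 221 / 0.8 = 276.25, so 277.

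The figure of 31 does not follow from these inputs. That is a separate defect, and nothing below depends on it. What matters here is that the only sizing in the article concerns HbA1c.

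**3. Error rate if either outcome may decide**

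Take one arm contrast and two outcomes, each tested at two-sided 0.05, with no true effect on either.

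- Independent outcomes: 1 − 0.95² = 1 − 0.9025 = 0.0975.
- Correlated outcomes (bivariate normal test statistics, simulated; correlations assumed because the article gives none): 9.5% at 0.3, 9.1% at 0.5, 8.3% at 0.7.

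Independence is the worst case for two-sided normal tests, so 9.75% is the upper limit. One fixed primary tested once gives 5%.

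**4. Which rules restore 5%**

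- One primary, with the other outcome tested only after it succeeds: at most 5%.
- Both outcomes must be significant, each at 0.05: at most 5%.
- Either may succeed with split alpha: 0.025 + 0.025 = 0.05 at most.

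**5. What the numbers can support if the liver outcome is primary**

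Evaluable per arm: 31 × 0.8 = 24.8, about 25. The standardised difference detectable with 80% power at two-sided 0.05, unadjusted, is (1.96 + 0.84) × √(2/25) = 2.80 × 0.283 = 0.79 SD by the normal approximation, and 0.81 SD with the t distribution.

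Statistical methods {20a} plans ANCOVA. Adjusting for the baseline value multiplies this by √(1 − r²), where r is the baseline correlation (assumed):

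- r = 0.5: 0.81 × 0.866 = 0.70 SD.
- r = 0.7: 0.81 × 0.714 = 0.58 SD.

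**The case against.** The best defence is that the trial was registered on 31 May 2023, before the first inclusion on 6 June 2023. One primary may be fixed in the registration, in Supplementary Table S1 or in an analysis plan, none of which is shown. That stands in part. A reader might infer that no primary is fixed anywhere, or that one will be picked after the results are known; the article shows neither. It shows a contradiction that leaves the choice open on paper. The defence does not remove the contradiction, because a primary fixed elsewhere would still leave at least two of the three sections wrong.

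Three stronger readings are tempting and should be set aside.

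- *More than two candidate outcomes.* FibroScan is used to "assess hepatic steatosis and fibrosis according to liver stiffness measurements (LSM) and controlled attenuation parameter (CAP) score", and glycaemic control has several measures, so a reader might count HbA1c, CAP and LSM as rival primaries. Supplementary Table S1 may say which reading defines severity. Only the conflict between glycaemia and liver is established.
- *A false-positive rate of 21% to 23%.* This results from testing two outcomes over all three pairwise arm contrasts. With a single outcome the same three contrasts already give about 12%, so roughly half of the figure comes from multiple arms and would survive a perfectly consistent primary. The article also does not state three unadjusted pairwise tests.
- *A detectable difference of no better than 0.81 SD.* That is the unadjusted value; the planned ANCOVA does better, as the last step of the working shows.

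**Conclusion.** Wrong as written. The Abstract, Outcomes {12} and Sample size {14} contradict each other on the primary outcome. The outcome that Outcomes {12} calls primary has no sample-size basis in the article, and the one that was sized is secondary there.

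The size attributable to this point alone is a rise from 5% to at most 9.75% on one contrast, or 8.3% to 9.5% at correlations of 0.7 to 0.3. It rests on three assumptions: two-sided tests at 0.05, two candidate outcomes, and either being allowed to decide. It is a risk that the text leaves open, not evidence of how the outcome will be chosen.

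The contradiction itself needs no assumption. It should be corrected before the data are examined, because it determines which hypothesis the trial tests.

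**What to change.** Issue a dated amendment, before the data are examined, that makes the Abstract, Outcomes {12} and Sample size {14} name the primary outcome registered before enrolment. The registration should govern, not a fresh choice: the trial is open, and recruitment was due to finish in December 2024. In particular, CAP should not be adopted by default, since Outcomes {12} does not name it.

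- If one primary is registered, test the other outcome as a key secondary only after the primary is significant on a named arm contrast.
- If both are registered as primary, state the rule: both must be significant, each at 0.05, or alpha is split, for example 0.025 each.
- In Sample size {14}, attach the statement to that primary. If it is the liver outcome, relabel HbA1c as secondary and give the liver difference detectable with about 25 evaluable per arm under the planned ANCOVA. The unadjusted value is 0.81 SD; the adjusted one will be smaller and should state its assumed correlation.

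The cost is an amendment to three sections and a check against the registration, with no change to trial operations. The price is that only one outcome, or one stated rule, can then carry the conclusion.

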### Participant timeline {13}

The participant timeline is shown in Table 1.

**Table 1 Tab1:**
[figure not shown]
Timeline

### Sample size {14}

The sample size was calculated according to changes in the primary outcome measure (12-week change in HbA1c with *α* = 0.05, *β* = 80%). A sample size of 31 individuals per group will be selected with mean changes of 0.4 and standard deviation of 1.5 and a 20% attrition rate [10]. It is calculated by PASS 15.

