### Methods/design {8}

The study is a randomized, single-center, parallel group, superiority clinical trial. All patients who meet eligibility criteria are invited to this study and then assigned to different groups with a 1:1:1 allocation rate, receiving 12 weeks of follow-up.

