## Assignment of interventions: allocation

### Random allocation sequence, concealment mechanism and implementation {16a} {16b} {16c}

Random numbers corresponded to the number of the 93 participants one by one that will be generated according to the table of random numbers. An independent researcher would arrange these random numbers from small to large. One to 31 are the lifestyle modification group, while 32–62 are designated as the metformin group, and 63–93 are the co-intervention group. The researcher responsible for recruitment will arrange subjects into the corresponding group according to the random numbers in an opaque envelope. Then, the endocrinologist and dietitian will provide the corresponding interventions.

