## Statistical methods

### Statistical methods for primary and secondary outcomes {20a}

All collected variables will be statistically analyzed by SPSS 28.0 statistical software and GraphPad Prism 8. Continuous variables will be assessed by analysis of covariance (ANCOVA). Categorical data will be assessed by the *χ*^2^ test. Differences between values within each arm will be evaluated using paired Student’s *t*‐tests. Nonparametric tests will be used to evaluate differences in non-normally distributed variables. Correlation analysis and multiple linear regression analysis will be used to analyze the synergistic effects of lifestyle modification and metformin. *P* < 0.05 will be used as the significance level.

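### The printed sample-size inputs (0.4, SD 1.5, α 0.05, 80% power, 20% attrition) do not give 31 per group; a two-sided two-group t-test needs about 278

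*Protocol article*

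**What the plan says.** The Sample size section says the number was "calculated according to changes in the primary outcome measure (12-week change in HbA1c", and gives the error rates as "12-week change in HbA1c with *α* = 0.05, *β* = 80" per cent. It then states that "31 individuals per group will be selected with mean changes of 0.4 and standard deviation of 1.5 and a 20% attrition rate", citing one source for the inputs and PASS 15 for the calculation.

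The Methods/design section describes a parallel-group superiority trial with participants "assigned to different groups with a 1:1:1 allocation rate". The allocation section carries the number forward: "One to 31 are the lifestyle modification group", with 32–62 and 63–93 for the other two groups, so the total is fixed at 93 = 3 × 31.

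The sample-size text does not state which groups are compared, which test was sized, whether it is one- or two-sided, or any baseline correlation. The statistical methods section plans ANCOVA for continuous variables at the 0.05 level, again without sidedness.

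**The concern.** The article prints all the main inputs and the result, so the calculation can be checked, and it fails by a factor of about nine. This is not a detail left to a fuller document.

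The number of patients is justified by this one calculation. If 0.4 and 1.5 are both right, the trial claims a power it does not have, and a null result would be read against that claim although it could not exclude the 0.4-point benefit. If one of the two figures is a misprint, the power may be roughly as claimed, but readers are shown the wrong planning assumption. The same sentence gives 80% as β, where 80% is plainly meant as the power and β is 20%.

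**Working it through.** **Inputs.** From the Sample size section: difference 0.4, SD 1.5, α 0.05, power 80% (printed as β), attrition 20%. From the Methods/design section: equal allocation to three groups. Assumed, because not stated: a two-sided test of two groups.

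**1. Attempt to reproduce 31.** Standardised difference: 0.4/1.5 = 0.267.

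Normal approximation: n = 2(1.960 + 0.842)² × (1.5/0.4)² = 2 × 7.849 × 14.06 = 220.7, so 221 per group. The exact noncentral t gives 221.7, so 222. With 20% attrition: 222/0.8 = 277.5, so 278 enrolled per group, or 834 in three groups. The plan has 31 and 93. The ratio is 278/31 ≈ 9.

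**2. What 31 per group provides.** After 20% loss, 31 × 0.8 = 24.8, about 25 evaluable. Exact t, two-sided, SD 1.5:

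| Evaluable per group | Power for 0.4 | Difference detectable with 80% power | 95% CI half-width |
|---|---|---|---|
| 25 | 15.2% | 1.21 | 0.85 |
| 31 (no loss) | 17.8% | 1.08 | 0.76 |

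The half-width is t × 1.5 × √(2/n). For n = 25 it is 2.011 × 1.5 × 0.283 = 0.85, about twice the 0.4 target.

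**3. Other readings of the same inputs** (α 0.05, 80% power unless noted):

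| Reading | Evaluable per group | Enrolled (÷ 0.8) |
|---|---|---|
| Two groups, one-sided | 175 | 219 |
| Within-arm paired, two-sided | 113 | 142 |
| Within-arm paired, one-sided | 89 | 112 |
| Three-group ANOVA, means 0, 0, 0.4 | 205 | 257 |
| Three-group ANOVA, means 0, 0.4, 0.8 | 69 | 87 |
| Three-group ANOVA, SD of the means = 0.4 | 47 | 59 |
| 0.4 taken as Cohen's f (SD ignored) | 22 | 28 |
| β = 80% taken literally (power 20%), two-sided | 36 | 45 |
| β = 80% taken literally, one-sided | 19 | 24 |

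None gives 31. At 25 evaluable, power is about 24% for the one-sided comparison and 25% for the two-sided paired test. A Bonferroni adjustment moves further away (337 enrolled for two comparisons, 370 for three).

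**4. ANCOVA.** If 1.5 were the SD of HbA1c itself rather than of its change, adjustment for baseline would multiply n by (1 − ρ²). To reach 25 evaluable, ρ = √(1 − 25/220.7) = 0.94. The section gives no correlation and presents the SD alongside a change, so this is a conditional check only.

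**5. Which inputs come near 31?** A standardised effect of 0.8, for example 0.4/0.5 or 1.2/1.5. The normal approximation gives 2 × 7.849/0.64 = 24.5. Divided by 0.8 this is 30.7, so 31; rounded to 25 first, it is 31.25. The exact t gives 25.5, so 26, and 26/0.8 = 32.5, so 33. Power at 25 evaluable is 79%. So 0.8 lands close to 31, but how exactly depends on the method and the rounding.

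**The case against.** The best counter-argument is that the sample size may be sound and only the printed inputs faulty. A standardised effect near 0.8 gives about 31 per group, with 79% power at 25 evaluable, so one wrong digit could explain everything. This stands as a possibility, and it limits what may be concluded.

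A reader might go further and infer that the SD is a misprint for 0.5, since 24.5/0.8 rounds up to 31. The documents do not support that. The match needs the normal approximation and division before rounding; the exact t gives 33. A difference of 1.2 with SD 1.5 fits just as well, and a different contrast or test could also lie behind the number. The cited source and the PASS output are not in the document. Equally, a reader might infer that the trial is shown to need 834 patients. That follows only if 0.4 and 1.5 are both what the authors intended, which is unknown.

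Two smaller points also stand. Two-sidedness is an assumption, but a one-sided test still needs 219 enrolled per group. And 25 evaluable is a simplification, because the plan is intention-to-treat with multiple imputation. Imputation cannot add more information than complete data on all 31 would hold, so 18% is the ceiling for the unadjusted two-sided comparison.

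The β label is a slip with an obvious meaning and adds no weight of its own.

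**Conclusion.** The point holds: the printed inputs and the printed sample size are incompatible. Taken at face value, with a two-sided two-group t-test assumed, the inputs call for about 222 evaluable (278 enrolled) per group, some nine times the plan. With 31 enrolled, power for 0.4 is 15% to 18%, and the difference detectable with 80% power is about 1.1 to 1.2 points, roughly three times the stated one. No alternative reading that was tried restores 31.

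Which figure is wrong (the difference, the SD or the contrast) cannot be settled from the document. The finding is that the stated calculation fails, not that a particular input was misprinted or that more patients are required. It must be fixed, because it is the trial's stated justification for its size.

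**What to change.** Reopen the PASS 15 run and the cited source, and print what was actually entered: the difference, the SD and what it refers to, the groups compared, the test and its sidedness.

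- If an input or the contrast was misprinted, correct it and show that the corrected set gives 31 after 20% attrition, or state the power that it does give. Where the 80% claim is kept, write it as power 80% (β = 20%).
- If 0.4 and 1.5 both stand, withdraw the 80% claim. State that 31 enrolled per group gives about 15% to 18% power for 0.4, and 80% power only for a difference of about 1.1 to 1.2 points, with the sidedness named.

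The cost is one paragraph in an amendment, and the stated power may become less favourable. No extra patients are requested.

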## Assignment of interventions: allocation

### Random allocation sequence, concealment mechanism and implementation {16a} {16b} {16c}

Random numbers corresponded to the number of the 93 participants one by one that will be generated according to the table of random numbers. An independent researcher would arrange these random numbers from small to large. One to 31 are the lifestyle modification group, while 32–62 are designated as the metformin group, and 63–93 are the co-intervention group. The researcher responsible for recruitment will arrange subjects into the corresponding group according to the random numbers in an opaque envelope. Then, the endocrinologist and dietitian will provide the corresponding interventions.

## Assignment of interventions: blinding

### Assignment of interventions: blinding {17a} {17b}

This trial is not blinded, so unblinding will not occur.

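### The trial is declared unblinded for everyone, which leaves the FibroScan reading behind the primary liver outcome open to detection bias that masking the operator would reduce

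*Protocol article*

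**What the plan says.** Under Assignment of interventions: blinding {17a} {17b}, the protocol article says "This trial is not blinded, so unblinding will not occur". Nothing else stands under that item, and no party is exempted.

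The Outcomes {12} section says "The primary outcomes are severity of NAFLD". The abstract is wider: "The primary outcomes are changes in glycemic control and severity of fatty liver from baseline to 12 weeks of follow-up". Both therefore make liver severity primary.

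The Hepatic steatosis section gives the instrument: "Transient elastography (FibroScan) would be performed after 8-h overnight fasting to assess hepatic steatosis and fibrosis", by liver stiffness (LSM) and controlled attenuation parameter (CAP). On timing it says "The severity of fatty liver will be evaluated at baseline and 12 weeks later". It does not say who operates the device or what that person knows.

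The Physical examination section has waist circumference measured at baseline and at 12 weeks, and blood pressure taken by sphygmomanometer at each visit. Both are secondary outcomes. Blood measures, including HbA1c, go to a central laboratory (Biochemical measurements for outcomes).

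**The concern.** Two different decisions have been merged. Whether participants and treating staff can be masked depends on the interventions, and here they cannot. Whether the person who measures the outcome is told the arm is a separate choice, and the plan makes it by default.

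It matters because a person, not an analyser, takes the FibroScan measurement. An operator who knows that a participant had the combined treatment may, without intent, obtain or accept readings that fit the expected benefit. That would be a systematic difference between arms in how the outcome is measured. ANCOVA adjusts for baseline and multiple imputation deals with missing values. Neither can separate a measurement shift tied to the arm from a treatment effect. More patients would not help either, because a fixed shift becomes easier to declare significant as the sample grows. Waist circumference and cuff blood pressure share the exposure, but as secondary outcomes.

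**Working it through.** **Step 1. Which outcomes are exposed.**

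| Outcome | Status in the article | How obtained | Exposure to knowledge of arm |
|---|---|---|---|
| Fatty liver severity (CAP/LSM) | Primary in the abstract and in {12} | FibroScan, operator not described | Yes |
| HbA1c | Secondary in {12}; called the primary outcome measure in Sample size {14}; glycemic control is primary in the abstract | Central laboratory | Much less |
| Waist, blood pressure | Secondary in {12} | Physical measurement, measurer not described | Yes |

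The blinding statement covers every row, but only the first and third depend on a person at the bedside.

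**Step 2. How much a reading shift could matter.** The plan gives no figure for assessor bias, so there is none of its own to reproduce. What follows is an illustration.

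Inputs:
- 31 per arm, from the allocation section ("One to 31 are the lifestyle modification group, while 32–62 are designated as the metformin group, and 63–93 are the co-intervention group"). With the 20% attrition in {14}, 31 × 0.8 = 24.8, taken as 25.
- Significance level 0.05, from {20a} (two-sided assumed).
- A spurious shift d in one arm, in units of the SD of the outcome, with no true difference. The values of d are assumptions; the documents give neither a shift nor an SD for CAP or LSM.
- A plain two-sample t-test, standing in for the planned ANCOVA. Under ANCOVA the same formula applies approximately, with d in units of the residual SD.

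The test statistic is non-central t with 2n − 2 degrees of freedom and non-centrality d × √(n/2). The false-positive rate is the probability that it falls outside the usual critical values, in either direction.

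For n = 31 and d = 0.25, the non-centrality is 0.25 × √15.5 = 0.98, there are 60 degrees of freedom, the critical value is 2.00, and the rejection probability is 16.2%.

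| Assumed shift | 31 per arm | 25 per arm |
|---|---|---|
| 0 | 5.0% | 5.0% |
| 0.05 SD | 5.4% | 5.3% |
| 0.10 SD | 6.7% | 6.4% |
| 0.25 SD | 16.2% | 13.9% |
| 0.40 SD | 34% | 28% |

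The result is driven by the assumed shift. At 0.05 SD the harm is negligible; at 0.25 SD the error rate is about three times nominal.

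**The case against.** **The article is condensed, so masked assessment may be in the full protocol.** This would carry weight if the article were silent. It is not: it declares the trial unblinded without exception, and a masked operator described elsewhere would contradict that declaration.

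**The article does not describe how an operator could influence a reading, and the size rests on assumed shifts.** This stands. The protocol does not show that the operator knows the arm or that readings are biased. It shows only that nothing prevents either. That is why a range is given and not a single rate.

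**The endpoint that fixed the sample size is HbA1c.** Also correct. Sample size {14} calls HbA1c change the primary outcome measure, and a central-laboratory value is much less open to this bias. The point is therefore limited mainly to the liver outcome, which two other sections name as primary.

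**A stronger reading concerns allocation.** The allocation section says "The researcher responsible for recruitment will arrange subjects into the corresponding group according to the random numbers in an opaque envelope", and a reader might infer that the recruiter can steer enrolment. The documents do not support this. The same section says "An independent researcher would arrange these random numbers from small to large", it uses opaque envelopes, and the consent section puts consent before assignment. It does not say who holds the envelopes. Whether they are sealed and sequentially numbered is detail that an article may leave to the full protocol. Applying an envelope assignment is not in itself a failure of concealment.

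**A reader might also infer that masking would eliminate the bias.** It would not. Participants may reveal their arm, and performance bias from open treatment remains.

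**Conclusion.** The concern holds for outcome assessment. As written, the plan leaves the FibroScan measure of a primary outcome, and the secondary waist and blood pressure measures, without protection against detection bias, although open treatment requires only participants and treating staff to be unmasked. The possible inflation of the false-positive rate runs from about 7% to 34% for shifts of 0.10 to 0.40 SD with 31 per arm. This assumes a shift in one arm, no true effect and a two-sided 5% test. The actual shift cannot be learned from the documents, and no direction is proven; a shift towards the expected benefit is the worrying case because the trial is a superiority trial. The HbA1c result is largely untouched. The change should be made, but the point does not show that the trial's results will be biased.

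**What to change.** Reword {17a} along these lines: the trial is open-label for participants and treating staff; the staff who perform FibroScan receive only a study number and are not told the arm; the same applies to those who measure waist and blood pressure where they are not the treating staff; participants are asked not to disclose their arm to the measurer; arms are coded A, B and C until the primary analysis is complete.

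The cost is wording and a coded request form. Sample size, visits and interventions do not change. No staff need be added, provided the existing FibroScan operator does not also treat the participants. The article does not say whether this is so; if the roles overlap, the scan would have to pass to a colleague. The downside is that a participant may occasionally break the masking.

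The Trial status section expected recruitment to end in December 2024, so the change may reach only the remaining 12-week scans and the analysis. For scans already done, the report should state whether the operator knew the arm.
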